## Results

The current study's findings will indicate that the application of herbal denture adhesive combined with essential oil will considerably improve the overall comfort of using the complete denture. It will reduce the bacterial growth and chances of mouth sores due to dentures. The expected results of the study indicate that the utilization of herbal denture adhesive combined with essential oil will increase the stability and retention of the dentures and the effectiveness of their retention over time.

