## Abstract

Introduction

The lack or complete loss of all-natural teeth is known as edentulism, and it happens frequently. One of the most prevalent issues among edentulous patients is severe resorption of the residual alveolar ridge, which can still occur even with cautious prosthetic treatment. Therefore, one of the biggest issues faced in dentistry today is retention and stability in the rehabilitation of completely edentulous patients using complete denture prostheses. This problem was resolved by using denture adhesives. Studies show that when denture adhesive is applied correctly, it improves stability and effectiveness for individuals wearing complete dentures by increasing the surface tension between the alveolar mucosa and the denture fitting surface. The denture adhesive must possess safety, cost-effectiveness, and sufficient antibacterial and antifungal properties. The application should be easy, without causing any mess, and have a pleasant smell. It should not alter or obstruct the denture's intaglio surface. Nowadays, it is acknowledged that denture adhesives are treatments that can be used in association with dentures.

Methods

Based on the type of denture adhesive, the patients will be randomly divided into two groups, i.e., 20 patients in each group: Group A (herbal denture adhesive without essential oil) and Group B (herbal denture adhesive with essential oil). The patients will be requested to fill out the questionnaire for masticatory efficiency, retention, stability, etc., at the time of denture insertion without using denture adhesive and seven days after the use of denture adhesive.

Expected results

The overall satisfaction of complete denture patients will be significantly increased when an herbal denture adhesive infused with essential oil is used. This will result in increased stability, retention of the mandibular denture, improved masticatory efficiency, and patient satisfaction.

Conclusions

Patients who are elderly may experience physical and psychological challenges when adjusting to new or relined dentures. Denture adhesive, however, can aid in the patient's satisfaction with the prosthesis' altered occlusion and fit. It also makes the patient feel more confident and secure. A dental professional must be consulted before using denture adhesive.

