## Materials and methods

Method

This experimental study will be conducted in the Department of Prosthodontics, Sharad Pawar Dental College and Hospital, Sawangi (M), Wardha, India. The data will be collected in the postgraduate clinic of the Department of Prosthodontics. On the basis of the inclusion and exclusion criteria (Table 1), the patients will be divided randomly into two groups: Group A (n=20) (herbal denture adhesive without essential oil) and Group B (n=20) (herbal denture adhesive with essential oil). A total of 16 closed-ended questions will be asked of patients: eight during denture insertion without using denture adhesives and eight questions seven days after using denture adhesives.

**Table 1 TAB1:** Inclusion and exclusion criteria

Inclusion Criteria	Exclusion Criteria
Patients who are first-time denture wearers	Patients with tooth-supported overdentures
Patients who are old complete denture wearers	Patients with implant-supported overdentures
Patients who are willing to participate in the study	Patients with a single complete denture

The denture adhesive will be fabricated by utilizing carboxymethylcellulose with flavor, mineral oil, petroleum, silica particles, and mesoporous nanoparticles of the selected essential oil (cinnamon oil) with antimicrobial action incorporated into a gel for prolonged release, giving better effectiveness. In order to gather information about denture fitting, removal, chewing, retention, and phonetics, a standard questionnaire form will be given to each patient. Following the patient's answer to Questionnaire 1 (Table 2), a clinical examination and application of denture adhesive demonstration will take place, adhering to the guidelines provided by the manufacturer. The patients will be provided with an explanation of the cleaning routine and the administration of denture adhesive for the next seven days. The patients will be contacted back a week later to complete an additional questionnaire (Table 3) in which they will be asked to rate the denture's strength, biocompatibility, convenience, and masticatory abilities using the glue that was provided.

**Table 2 TAB2:** Questionnaire 1 (at the time of denture insertion) Reference: [1,6,7]

Sr. No.	Questions	Options	No. of Patients
1.	To what extent do you find the retention of your upper denture satisfactory?	Dissatisfied	
		Neutral	
		Satisfied	
2.	To what extent do you find the retention of your lower denture satisfactory?	Dissatisfied	
		Neutral	

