		Satisfied	
3.	To what extent do you find the chewing ability of your denture satisfactory?	Dissatisfied	
		Neutral	
		Satisfied	
4.	To what extent are you happy with the comfort of your new denture?	Dissatisfied	
		Neutral	
		Satisfied	
5.	To what extent do you find the speech and sound produced by the denture satisfactory?	Dissatisfied	
		Neutral	
		Satisfied	
6.	How satisfied are you with the way your dentures fit and removal?	Dissatisfied	
		Neutral	
		Satisfied	
7.	Does your denture harm the soft tissues in any way?	Yes	
		No	
8.	Do you have any issues with swallowing because of the denture?	Yes	
		No	

**Table 3 TAB3:** Questionnaire 2 (after seven days of denture insertion) Reference: [1,6,7]

Sr. No.	Questions	Options	No. of Patients
1.	To what extent are you satisfied with the adhesive's ability to keep your upper denture in place?	Dissatisfied	
		Neutral	
		Satisfied	
2.	To what extent are you satisfied with the adhesive's ability to keep your lower denture in place?	Dissatisfied	
		Neutral	
		Satisfied	
3.	How was your chewing experience after using this denture adhesive?	Worse	
		No difference	
		Better	
4.	For what duration did the denture adhesive work on your dentures?	≤4 hours	
		4-8 hours	
		8-12 hours	
5.	How does this denture adhesive taste?	Bad	
		Neither good nor bad	
		Good	
6.	How did you find it to remove the adhesive from your dentures?	Difficult	
		Neutral	
		Easy	
7.	How did you find it difficult to clean your denture after using the denture adhesive?	Difficult	
		Neutral	
		Easy	
8.	How difficult was it for you to wipe your oral cavity after using the denture adhesive?	Difficult	
		Neutral	
		Easy	

Sample Size

The sample size is determined using the following formula: n = {(Z 1-α/2 + Z 1-β)2 p1(1-p1) + p2 (1-p2)}/(p1-p2)^2^, where the proportion of outcome from group 1 (p1) = 0.37, the proportion of outcome from group 2 (p2) = 0.22, the level of significance (α) = 0.05, power (1-β) = 0.80, Z alpha value = 1.96, Z beta value = 0.84, and the total sample size = 40. The sample size estimation is done at a 95% confidence interval. Each group consists of 20 samples.

Statistical analysis

The statistical analysis will be done using IBM SPSS Statistics for Windows, Version 23 (Released 2015; IBM Corp., Armonk, New York). Descriptive statistics will be used for the mean distribution of both groups, and an independent sample t-test will be used for intergroup analysis between both groups.

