A study by Ereifej et al. surveyed 64 edentulous patients for the first time, comparing their satisfaction with denture adhesives. The patients were divided into three groups, each receiving a complete denture prosthesis. After a month, they rated their satisfaction on a 100 mm Visual Analog Scale (VAS) scale and completed an oral health impact profile questionnaire. The study found that all groups had significantly higher VAS values and lower OHIP-EDENT scores after applying the adhesives. However, the ease of cleaning was significantly different between groups. The study concluded that denture adhesives improved patient satisfaction and standard of living [9].

Study limitation

The present study is conducted to create a novel herbal denture glue that contains essential oil and can reduce bacterial count while also being more advantageous to patients in retention, stability, enhancing mastication, and esthetics. However, the study's sample size and short duration limit the generalizability of the findings. Further research with larger sample sizes and longer follow-up periods is recommended to confirm these results and assess long-term effects.

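### Comfort, mouth sores and bacterial growth are promised as results, and biocompatibility as a day-7 rating, but the printed day-7 questionnaire covers none of them

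*Protocol article*

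**What the plan says.** **Claims.** The Results section of the protocol article sets out what the findings will show for the essential-oil adhesive:
- It "will considerably improve the overall comfort of using the complete denture".
- On bacteria and sores: "It will reduce the bacterial growth and chances of mouth sores due to dentures".
- It "will increase the stability and retention of the dentures and the effectiveness of their retention over time".

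The Study limitation paragraph of the Discussion describes the product as one that "can reduce bacterial count while also being more advantageous to patients in retention, stability, enhancing mastication, and esthetics".

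**Promised content of the questionnaires.** The Abstract says patients will "fill out the questionnaire for masticatory efficiency, retention, stability, etc., at the time of denture insertion", and again after seven days of adhesive use. The Method text says that at one week patients will use Table 3 to "rate the denture's strength, biocompatibility, convenience, and masticatory abilities using the glue that was provided".

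**Data described.** There are 16 closed-ended questions, eight before adhesive (Table 2) and eight at day 7 (Table 3). One clinical examination is mentioned. It follows Questionnaire 1 and accompanies the adhesive demonstration. Table 2 item 7 asks "Does your denture harm the soft tissues in any way", and item 8 asks about swallowing problems.

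**The concern.** The two groups differ in the essential oil, which the Method text describes as cinnamon-oil nanoparticles with antimicrobial action in a prolonged-release gel. The questions most specific to the A-versus-B comparison are therefore whether the oil affects bacteria and how the mucosa tolerates it. The plan predicts a favourable answer to both, yet the printed day-7 instrument asks about neither.

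Comfort, the first benefit named in the Results section, is in the same position: asked at insertion and not again. If the day-7 contact passes without these items, no analysis can recover them. The expected statements could then be neither supported nor refuted from the questionnaires, and the essential-oil product could be reported as beneficial without comparative patient-reported tolerability.

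**Working it through.** The plan states no figure for this point, so there is none to reproduce. The check is an item-by-item match of the two printed questionnaires and then of each claim against them.

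**Step 1. Topics at each time.**

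| Questionnaire 1 (before adhesive) | Asked again at day 7? |
|---|---|
| 1 Upper retention | Yes (item 1) |
| 2 Lower retention | Yes (item 2) |
| 3 Chewing | Yes (item 3) |
| 4 Comfort | No |
| 5 Speech | No |
| 6 Denture fit and removal | No |
| 7 Soft-tissue harm | No |
| 8 Swallowing | No |

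Three of eight topics recur and 8 − 3 = 5 do not. The other five day-7 items are new: duration of effect, taste, removing the adhesive, cleaning the denture and cleaning the mouth. Item 6 of Table 3 concerns removal of the adhesive, so it does not repeat item 6 of Table 2.

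**Step 2. Claims against data.**

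| Claim or promised rating | Where stated | Before adhesive | Day 7 |
|---|---|---|---|
| Comfort | Results | Item 4 | None |
| Bacterial growth | Results | None | None |
| Mouth sores | Results | Item 7, as a proxy | None |
| Biocompatibility (to be rated) | Method | Not applicable | None, although Table 3 is named as the place |
| Stability | Abstract, Results | No item names it | Items 1 and 2, at most a proxy |
| Retention | Results | Items 1 and 2 | Items 1 and 2 |

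The clearest contradiction is in the biocompatibility row: the Method text points to Table 3 for a rating that Table 3 does not contain. On stability, Table 3 asks how well the adhesive holds each denture in place. That may reflect stability in part, but the Results section names stability and retention as two effects, and these items cannot separate them.

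**Step 3. What a repeated harm item could show with 20 per group.** With no events in n patients, the exact two-sided 95% upper limit is 1 − 0.025^(1/n). For n = 20 this is 1 − 0.025^(1/20) = 1 − 0.832 = 0.168, or about 17%. A clean result in one group would still be compatible with a true rate of up to roughly one patient in six.

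**The case against.** The best defence is that the stated aim, in the Introduction, is patient satisfaction with denture retention, and Table 3 items 1 and 2 measure that after adhesive use. The bacterial and sore statements are expectations in prose. They are not declared endpoints, and no planned test depends on them. The two forms also serve different purposes: one rates the denture and the other the adhesive. This stands, and it limits the point to a mismatch between claims and instrument. It does not remove the mismatch, because the Results section presents these effects as what the findings will indicate, and the biocompatibility sentence is a statement of method.

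A reader might infer more than the documents support:
- **That better biocompatibility is claimed.** It is not. The text only says it will be rated.
- **That stability is wholly unmeasured.** The two in-place items are a loose proxy.
- **That better esthetics is an expected result.** It appears only in the product description under Study limitation.
- **That the Conclusions are unsupported on these points.** They make none of these claims.
- **That a tissue reaction would go unrecorded.** This is a condensed article. Adverse-event recording and examination at follow-up may be in the full protocol, which is not shown. Only the content of the questionnaires can be judged.
- **That harm items were deliberately removed.** The documents show only that the two forms differ.

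**Conclusion.** The point holds as a contradiction within the article. Comfort, bacterial growth and mouth sores are presented as results to come, and biocompatibility as a day-7 rating. None of the four has a day-7 item or measure, and bacteria are measured at neither time. Questionnaire 1 items 4, 7 and 8 have no post-adhesive counterpart, and stability is not separable from retention. The questionnaires therefore give no A-versus-B data after adhesive use on these claims or on tolerability of the essential-oil product.

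This rests on Tables 2 and 3 being the complete instruments, which the stated count of eight plus eight questions supports. It does not rest on any assumption about safety recording outside the questionnaires. The comparison of retention satisfaction is not affected.

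**What to change.** 1. **Questionnaire 2.** Repeat Questionnaire 1 items 4 (comfort), 7 (soft-tissue harm) and 8 (swallowing) for both groups, worded to refer to the period of adhesive use. The present item 7 asks about harm from the denture, so repeating it verbatim would not direct the patient to the adhesive period. This also puts an item behind the biocompatibility sentence in the Method text.
2. **Analysis.** Report items 7 and 8 for A versus B as counts with a risk difference and exact 95% CI. State that 20 per group gives only weak evidence on tolerability. Comfort can follow the chi-square or Fisher test already planned for qualitative variables.
3. **Claims.** Remove the bacterial-growth statement from the Results section and the bacterial-count and esthetics statements from Study limitation, or label them as not assessed. In the Abstract and the Results section, describe stability as not assessed separately from retention.
4. **Consistency.** Questionnaire 2 would have 8 + 3 = 11 items and the total would be 16 + 3 = 19. Since overall satisfaction is taken from each questionnaire's total score, state whether the added items count towards it.

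The cost is three short questions at a contact that already takes place, and narrower claims. The items must be in place before the day-7 contacts, because the answers cannot be obtained afterwards.

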## Discussion

Denture adhesives are categorized based on how they are manufactured, such as powder, tapes, gels, and paste. Denture adhesive enhances retention, lessens denture soreness, avoids strangling the mucosal blood supply, and lessens the need for adjustments even when the denture fits.

A study by Mekkawy et al. involved 30 edentulous patients who were divided into two groups and given various types of denture adhesives (SECURE and COREGA) for seven days. The patients' satisfaction with denture retention, chewing ability, stability, and efficiency were assessed. The study found that the prosthetic denture adhesives significantly improved denture retention in the mandible and the duration of the adhesion in the mouth. However, there was no significant increase in the ability to remove the adhesive or maxillary denture retention. The study suggests that effective use of denture adhesives requires patient education and proper dental guidance [1].

A study by Yadav et al. involved 30 edentulous patients with resorbed ridges. They used isabgol, fixon powder, and Fittydent powder denture adhesives. Incisal bite force and retention force were measured using FlexiForce sensors (Tekscan, Massachusetts) and digital force gauges. Fittydent powder and isabgol significantly increased retention and biting force compared to fixon [4].

A study by Koronis et al. involved 30 edentulous patients who had their denture-supporting tissues and old dentures renewed. They were prescribed three different brands of denture adhesives: Fittydent, Seabond, and Protefix. The adhesives were used for 48 hours on the lower denture, with participants spending 24 hours without adhesives. The results showed that denture adhesives generally enhance patient satisfaction and chewing ability, especially in those with poor Kapur index and poor denture retention. Fittydent was found to be the most effective adhesive [8].

A study by Ereifej et al. surveyed 64 edentulous patients for the first time, comparing their satisfaction with denture adhesives. The patients were divided into three groups, each receiving a complete denture prosthesis. After a month, they rated their satisfaction on a 100 mm Visual Analog Scale (VAS) scale and completed an oral health impact profile questionnaire. The study found that all groups had significantly higher VAS values and lower OHIP-EDENT scores after applying the adhesives. However, the ease of cleaning was significantly different between groups. The study concluded that denture adhesives improved patient satisfaction and standard of living [9].

Study limitation

The present study is conducted to create a novel herbal denture glue that contains essential oil and can reduce bacterial count while also being more advantageous to patients in retention, stability, enhancing mastication, and esthetics. However, the study's sample size and short duration limit the generalizability of the findings. Further research with larger sample sizes and longer follow-up periods is recommended to confirm these results and assess long-term effects.

## Conclusions

Patients who are elderly may experience physical and psychological challenges when adjusting to new or relined dentures. Denture adhesive, however, can aid in the patient's acclimatization to the prosthesis. It also makes the patient feel more confident and secure. A dental professional must be consulted before using denture adhesives.
